## Abstract

**Background:**

An open, constructive safety culture is key in healthcare since it is seen as a main condition for patient safety. Studies have examined culture improvement strategies in hospitals. In primary care, however, not much is known about effective strategies to improve the safety culture yet. The purpose of this study is to examine the effect of two patient safety culture interventions: a patient safety culture questionnaire solely, the SCOPE, or the SCOPE questionnaire combined with a patient safety workshop. The purpose of this paper is to describe the rationale and design of this trial.

**Methods/design:**

The SCOPE Intervention Study is a cluster randomized, three-armed controlled trial, that will be conducted in 30 general practices in the Netherlands. Ten practices in the first intervention arm will complete the SCOPE questionnaire and are expected to draw and implement their own improvement initiatives based on a computerised feedback report. In the second intervention arm, staff of the ten practices also will be asked to complete the SCOPE questionnaire and in addition will be given a complementary workshop. This workshop is theoretical and interactive, educating staff and facilitating discussion, leading to a practice specific action plan for patient safety improvement. The results of the SCOPE questionnaire are incorporated in the workshop. The ten practices in the control arm continue care as usual. Baseline and follow-up measurements will be conducted with an implementation period of one year. The primary outcome will include the number of incidents reported and secondary several quality and safety indicators and the patient safety culture. Moreover, interviews will be conducted at follow-up to evaluate the implementation process of the intervention.

**Discussion:**

Results of this study will give insight in the effect of administering a culture questionnaire or the questionnaire with a complementary workshop. This knowledge will aid implementation of patient safety tools and future research. Attention has been given to the strengths and limitations of the study.

**Trial registration:**

Netherlands Trial Register: NTR3277.

## Background

A main condition for patient safety is an open constructive safety culture. Patient safety culture is described as the values, attitudes, norms, beliefs, practices, policies, and behaviours regarding safety issues in daily practice [1]. One of the main recommendations in the Institute of Medicine report ‘to Err is Human’ was to support a safety culture. The National Patient Safety Agency in the UK also recognizes the importance of an open culture. In their developed "Seven steps to patient safety for primary care" the first step is to "build a safety culture" [2]. In a report about safety in healthcare in the Netherlands, the former director of Shell, called an environment where acknowledging mistakes is taboo, one of the main causes of safety-risks [3]. Non-medical industries have been working on safety for much longer and showed that an open culture on error ameliorates business performance [4,5]. Reports suggest a similar role of safety culture in healthcare [6,7].

In hospital care, team training and communication, executive walkrounds and Comprehensive Unit-Based Safety Program (CUSP) are well received interventions to improve patient safety culture that have been studied. Although positive effects were reported, the level of evidence moderates firm conclusions on the effectiveness of patient safety culture in healthcare [8,9]. Despite the fact that a large part of healthcare is delivered in primary care where practice organisations are becoming larger scaled and more complex, leading to increasing importance of patient safety issues, the effectiveness of such improvement strategies in primary care is underexposed.

Often, the first step to initiate patient safety culture improvements is to measure the current state of affairs. We have developed and validated a patient safety culture questionnaire for general practice: the SCOPE [10]. During this former study we observed that this culture questionnaire raised awareness and stimulated some professionals to change their practice. The conducting of a survey can be perceived as a measurement tool and also as a vehicle for communication. It is stated that the actual administration of a survey operates as an intervention. The survey affects people’s perceptions and sends messages to employees about the importance of the topic it addresses [11]. Also, feedback of patient safety culture surveys, combined with benchmark data are found highly informative [12]. Others observed a possible intervention effect of conducting a culture questionnaire [9,13,14].

However, it is not clear what the magnitude and the sustainability of the application of a single questionnaire is. It appears that professionals find it difficult to shape actual improvement in practice [15]. We expect that the effect of a single questionnaire could only be temporarily, and subsequently, that the raised awareness will fade away and thus will not lead to actual safety culture improvements. Sexton et. al developed a tool to discuss results of a culture questionnaire as they state that without such a tool it would be unlikely that spontaneous discussions lead to meaningful improvements in cultures, given the relative novelty of safety culture and its complexity [16]. This corresponds to the reasoning that “the process of reporting results is perhaps most important in determining a survey’s effectiveness as a cultural change tool” [11]. Hence, a more practical and comprehensive intervention seems needed for obtaining profound and lasting results. Following this, we develop a complementary workshop to the SCOPE questionnaire, based on the Manchester Patient Safety Framework (MaPSaF) [17]. The MaPSaF is developed by the NHS specifically for primary care. The tool aims at helping primary care practices to assess the current level of maturity (pathological, reactive, bureaucratic, proactive, generative) of their approach to patient safety. The tool’s output serves as a basis for discussions on how to improve the practices’ patient safety. Our approach resembles the CUSP, an eight step programme to improve safety culture, used in hospitals [18]. The first step is to measure the culture, followed by the science of safety, identification of safety concerns by staff, adopting of a unit by senior executives, implementation of improvements, analysing and documentation of efforts, sharing of results and last, reassessment of culture.

### Objectives

The first objective of this study is to examine the effect of two interventions on patient safety behaviour and patient safety culture in general practice: the SCOPE questionnaire solely, and the SCOPE questionnaire combined with a safety culture workshop. We conduct a three armed trial instead of a two-armed trial. The purpose of the ‘questionnaire only’ arm is twofold. Firstly, to assess whether administering a culture questionnaire with only a feedback report has an effect on patient safety behaviour and culture, compared to the control arm. Secondly, to be able to adjust for the possible intervention effect of the questionnaire in the workshop arm.

Our second objective is to evaluate the implementation process of both interventions. Designing, implementing and evaluating a patient safety culture intervention is complex. The direction of results will largely depend on the context [19-22]. Therefore, evenly important as the possible effect of the interventions is the process evaluation.

## Methods/design

### Design and setting

The SCOPE Intervention Study is a cluster randomized, three-armed controlled trial complemented with a qualitative study. The study will be conducted in thirty general practices in the Netherlands.

### Practices selection and randomization

All general practices (n = 350) in Utrecht area receive an invitation to participate in the study. Practices that consist of at least three employees of whom at least one GP can participate in the study. In addition, the SCOPE questionnaire should not have been completed in the past two years. Stratified randomization will be used to allocate the practices in the three trial arms (see Figure 1). Stratification is based on practice size and whether a practice is accredited on the Dutch GP Practice Accreditation system [23], as we expect these parameters to possibly confound the effects on patient safety culture. The randomisation will be performed by the Data Management Unit of the Julius Center, independent of the research team. Because of the nature of the intervention blinding is not feasible.

**Figure 1 F1:**
[figure not shown]
Flowchart randomisation.

### Procedure

In Figure 2 an overview is given of the intervention procedure and timeframe. Practices in the control arm continue work as usual. All practices are asked to complete a baseline and follow-up questionnaire. At follow-up we administer the SCOPE questionnaire to all participating practices and we will carry out interviews.

**Figure 2 F2:**
[figure not shown]
Flowchart of study procedure.

#### Intervention arm I

Practices allocated to intervention I receive access to the online SCOPE questionnaire and simultaneously receive a key to download their results in a feedback report. Also, it is communicated that they are expected to anticipate on these results themselves. After one week a reminder is sent. Additionally, one month after the reminder an email is sent reminding the practice of the feedback report and to inform them about the continuation of the study. We interfere as little as possible in this research arm trying to mimic the normal course of events, when a practice would choose for itself to use the SCOPE questionnaire as improvement strategy.

#### Intervention arm II

The practices in intervention II also receive access to the questionnaire. However, these practices do not receive the key to download their results. Instead, they will be given a patient safety workshop at their practice location. The feedback on the results of their questionnaire is embedded in this workshop. The complete feedback report is handed out at the end of the workshop.

### Interventions

The intervention consists of the SCOPE questionnaire solely (intervention I) or the SCOPE combined with a patient safety workshop (intervention II). We chose the SCOPE questionnaire and the workshop for both practical and theoretical reasons. The European Linneaus project recommends the AHRQ safety culture questionnaire, from which the SCOPE has been derived, and the MaPSaF for primary care [17,24]. The SCOPE questionnaire and the Dutch translation of the MaPSaF were both readily available and translated in Dutch. In addition, the tools combine well together as the dimensions largely correspond with each other, facilitating the alignment of the workshop as complementary to the questionnaire.

### SCOPE questionnaire

The SCOPE questionnaire is a culture questionnaire for general practices. The SCOPE is derived from the HSOPS and validated in Dutch general practice [10,25,26]. Chronbach’s alpha ranged between 0.64 - 0.85. The questionnaire consists of 43 items divided over eight dimensions:

(1) Handover and teamwork (8 items)

(2) Support and fellowship (5 items)

(3) Communication openness (6 items)

(4) Feedback about and learning from error (6 items)

(5) Intention to report events (3 items)

(6) Adequate procedures and adequate staffing (7 items)

(7) Overall perceptions of patient safety management (4 items)

(8) Expectations and actions of managers (4 items).

Items are answered using a five point scale varying from ‘strongly disagree’ to ‘strongly agree’ or ‘never’ to ‘always’. In addition, respondents are asked to grade the patient safety culture in their practice. Also, questions on demographics such as gender, age and years of working experience are included. All staff of each practice are asked to complete this questionnaire. For data collection and storage an online system will be used, managed by the Dutch GP Practices Accreditation Organisation [23].

#### SCOPE feedback report

Results of the completed questionnaires are presented in a computerized feedback report. In this report it is presented how often the questionnaire is completed and by which disciplines. Per dimension the percentage positive scores (four or five on the five point-scale) are calculated. When this is 75 percent or higher it is perceived as a “strong” dimension. When this percentage is lower than 50 percent it is perceived as a “weak” dimension and, when scored in between it is “neutral”. The eight dimensions, the percentage positive scores and their classification are presented in a table. Subsequently, all complete dimensions with all questions are reported. Per question the average practice score is reported and compared with an overall benchmark mean that is calculated from data of all practices that have completed the SCOPE questionnaire in 2008 (n = 506-587). When a question scores more than fifteen percent lower than this mean it is depicted red and when higher green. By this, practices can inform themselves on their performance being average, below or above, as compared to the benchmark average. The last page of the report gives general suggestions to improve the patient safety in practice. Suggestions are not fully worked out, but address some issues and refer to more reading material and organizations that can be consulted, if desired. The feedback report is downloaded from the same webpage as where the questionnaires are completed.

### Workshop

The workshop is based on the Dutch translation of the MaPSaF [27]. The MaPSaF is a matrix of nine dimensions in which for each dimension all five maturity stages (pathological, reactive, bureaucratic, proactive, generative) of patient safety are described. We add items on theory on patient safety, human factors engineering and safety culture.

The workshops are organized at each practice location to make it easier for staff to attend. It requires three and a half hour and at least 75% of the staff should be present.

The workshops are given by both an educational scientist who also is a GP and one of the researchers (NV). We intentionally chose for one of the trainers to be an outsider of the research project as well as to be a GP. The first feature allows for questioning and interpreting independently of the research project. The second feature, the trainer being a GP, may allow more rapidly gaining a certain level of understanding and trust among the participants because of being familiar with the GP’s practice and context. We believe that the content of the workshop will be better conveyed when explained by a GP. In addition, as the dialogues can contain intimate content, for example when discussing an incident or flaws in communication between staff, a GP as trainer may be easier to confide in and can also display more understanding of the situation. The researcher attending the workshop gives the opportunity to observe and gather research data. Being part of the research setting is linked with intimate knowledge of the situation, which is essential to develop an understanding ‘from within’.

#### Workshop programme

 ▪ Introduction to patient safety

 – Discussing patient safety terminology

 – Data on number of incidents internationally and nationally

▪ Human factor engineering

 – Why do people make mistakes

 – Interactive examples

 – System approach

▪ Classify organization according to the MaPSaF vignettes on two dimensions (individually)

 – Each respondent classified the maturity of their practice for two dimensions without consultation

▪ Patient safety culture

 – Theory on patient safety culture

▪ Feedback on SCOPE questionnaire

 – Discussion about results

▪ Dialogue about own patient safety culture based on vignettes

 – Vignettes are discussed in pairs (trying to align with each other)

 – Vignettes are discussed with all staff

▪ Brainstorm on possible improvement actions

▪ Drafting of practice improvement action plan

▪ Evaluation & take home message

The workshop is both theoretical and interactive, facilitating discussion among practice staff about their own safety culture. In consecutive order we cover an introduction to patient safety, including discussion about terminology and international and national data about patient safety incident numbers. Followed by theory and interactive examples of human factor engineering and a systems approach to error. Subsequently, we ask all staff to classify the maturity stage, following the MaPSaF matrix, on two vignettes. A vignette is an A4-paper with one dimension worked out in five descriptions of this patient safety theme according to the five stadia. Staff are asked to choose the description that resembles their own daily practice the most. Per workshop we discuss two dimensions: the dimensions that scores the lowest on the SCOPE questionnaire. To be sure the same vignettes will be used for the same SCOPE dimension we made a compatibility table of the SCOPE dimensions and the MaPSaF dimensions (Table 1). The first two SCOPE dimensions have the same MaPSaF dimension. When these are the weakest dimensions, we will use the three weakest SCOPE dimensions in order to have two different vignettes to discuss. The two vignettes in each practice will be different dependent on their SCOPE results.

**Table 1 T1:** Compatibility table of SCOPE questionnaire and MaPSaF dimensions

**SCOPE**	**MaPSaF***
Handover and teamwork	Teamwork
Support and fellowship	Teamwork
Communication openness	Communication about patient safety
Feedback and learning from error	Learning from errors and achievement of improvement
Intention to report events	Registration and evaluation of errors
Adequate procedures and adequate staffing	Personnel management and safety issues (Resources)
Overall perceptions of patients safety management	Priority given to patient safety (Staff education and training aimed at patient safety)
Expectations and actions of managers	Errors and responsibility for patient safety

*Dutch version of MaPSaF.

After scoring these vignettes we introduce theory on culture as an important aspect of patient safety. Subsequently, we show the practice results on their SCOPE questionnaires at dimension levels and ask whether these are recognized and discuss these. Next, we will ask to discuss the MaPSaF vignettes in pairs and subsequently in the whole group. During the workshop we facilitate discussion about the patient safety culture of the practice using the results of the SCOPE, the vignettes and other themes that emerge, leading to a brainstorm of possible improvements. At the end of the workshop the staff will draw a practice specific improvement plan. The workshop ends with an evaluation and a round with take home messages from everyone.

#### Pretesting workshop

The workshop has been piloted during a training day in six general practices. The aim of this pilot was twofold, first to evaluate the workshop and to be able to customize possible improvements. Second, to give the trainers a chance to get acquainted to the programme. The workshop was well received, main adjustments were to print out a format for the action plan to take home and to print out the feedback report and handing them out directly after the workshop instead of e-mailing them afterwards.

#### Facultative workshops after ending the study

During the recruiting of the practices, we will communicate that a facultative workshop will be offered for all practices allocated to the control and intervention I arm after ending the study. Hereby, we aim to prevent selective drop-out of practices in the control and intervention I arm.

### Measurements

#### a. Patient safety behaviour

The primary endpoint is the number of incident reports reported by staff in the practice. This endpoint is chosen as incident reporting gives an indication of the patient safety behaviour and culture in the practice. We hypothesize that an increase of reported incidents corresponds to an open patient safety culture. Secondary endpoints are the presence of quality and safety indicators in the previous year such as ‘the presence of a procedure for complaints’, ‘how often safety was on the agenda and/or discussed during team meetings’, ‘whether a safety management policy was present’ and ‘whether safety was subject of staff education’. These outcomes are measured using a practice questionnaire at baseline and follow-up in all study arms.

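### The staff-education endpoint overlaps with the arm II workshop, so a yes in that arm at follow-up may record delivery of the intervention rather than changed behaviour

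*Protocol article*

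**What the plan says.** Under Measurements, a. Patient safety behaviour, the secondary endpoints are "the presence of quality and safety indicators in the previous year". The examples include "whether safety was subject of staff education" and "how often safety was on the agenda and/or discussed during team meetings". On collection, the article states: "These outcomes are measured using a practice questionnaire at baseline and follow-up in all study arms".

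The Abstract (Methods/design) describes what arm II receives: "This workshop is theoretical and interactive, educating staff and facilitating discussion, leading to a practice specific action plan for patient safety improvement". The Workshop section gives its length and reach: "It requires three and a half hour and at least 75% of the staff should be present". The Workshop programme lists theory on patient safety, human factors and safety culture, and includes the step "Vignettes are discussed with all staff". Under Facultative workshops after ending the study, control and arm I practices are offered the workshop only once the study is over.

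On timing, the Abstract states: "Baseline and follow-up measurements will be conducted with an implementation period of one year". Data analysis says that the quality and safety indicators will be described and that baseline will be compared with follow-up.

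**The concern.** The education item asks whether something took place in the practice during the past year. In arm II the study itself makes that thing take place. A practice that received the workshop and did nothing afterwards could answer yes and be correct. In the other two arms a yes has to come from activity outside the study workshop.

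The first objective is the effect on patient safety behaviour, and the Discussion says the trial will show whether the workshop adds to that effect. If the education item is shown as one of the behaviour results, a rise in arm II may look like behaviour change when it only confirms that the workshop was held. Both possible readings carry the problem: baseline against follow-up within arm II, and arm II against the other arms.

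**Working it through.** **The plan's own figure.** The article gives no figure for these indicators. Its only related figure is a power of 0.90 for the primary endpoint. A one-way analysis of variance on means 50, 70 and 100 (SD 30, 10 practices per arm, alpha 0.05) has grand mean 73.33 and noncentrality 10 × (544.4 + 11.1 + 711.1)/900 = 14.07. With 2 and 27 degrees of freedom the power is 0.898, so the stated figure is reproduced. It concerns incident reports, and the present point does not touch it.

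**Timing.** The workshop uses the practice's SCOPE results, so it follows SCOPE completion and precedes follow-up. If the one-year implementation period runs from baseline, the workshop lies inside the follow-up look-back year. If it runs from the workshop, the workshop lies at the edge of that year or just outside. Figure 2, which gives the timeframe, is not shown. Inside the window is likely, but it is an assumption.

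**Education item.** Assume that the workshop is inside the window, is counted, and is delivered to all 10 arm II practices without drop-out. Arm II is then 10/10 at follow-up whatever its staff do later. Let *p* be the control yes rate (not in the article).

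- Built-in difference from control = 1 − *p*.
- Rise within arm II = 1 − *b*, where *b* is its baseline yes rate (also not given). A practice already at yes cannot rise.
- Illustrative two-sided Fisher p for 10/10 against *x*/10 = 2 × C(10, 10−*x*)/C(20, 10−*x*).

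The Fisher values are:

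- 10/10 against 3/10: 2 × 120/77520 = 0.003
- 10/10 against 5/10: 2 × 252/15504 = 0.03
- 10/10 against 7/10: 2 × 120/1140 = 0.21

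The p-value is below 0.05 when control has at most 5 of 10 at yes. The binomial probability of that gives the last column.

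| Assumed control yes rate | Built-in difference (points) | Chance of Fisher p < 0.05 from delivery alone |
|---|---|---|
| 0.1 | 90 | 1.00 |
| 0.3 | 70 | 0.95 |
| 0.5 | 50 | 0.62 |
| 0.7 | 30 | 0.15 |
| 0.9 | 10 | 0.002 |

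These values only show scale. No such test is planned for the indicators.

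**Team-meeting item.** This is a frequency. One workshop adds at most 1 to a yearly count *k*, a relative change of 1/*k*: 100% for *k* = 1, 50% for 2, 25% for 4, 17% for 6 and 8% for 12 (counts assumed). The addition occurs only if the respondent regards the workshop as a team meeting.

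**The case against.** A reader might infer something stronger: that the workshop satisfies both the education and the team-meeting endpoints, so that arm II is bound to improve. The documents do not support that.

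- The meeting item asks how often. One session cannot satisfy it, and the article nowhere calls the workshop a team meeting.
- Practices already at yes for education have no room to rise. The Discussion expects motivated practices to volunteer, so a high starting rate is plausible.
- The position of the workshop in the look-back year is not confirmed.

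Each of these limits stands.

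It can also be said that the questionnaire is not shown. The article only paraphrases its items, and the form may already tell practices to leave out study sessions. That lowers confidence but does not remove the point. The endpoint and the intervention coincide as the article states both, and it mentions no exclusion. Elsewhere the authors do deal with such an overlap: under b. Patient safety culture they discuss SCOPE as both intervention and measurement tool. They say nothing similar about the workshop and this item.

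Finally, the indicators are secondary and analysed descriptively, and the interviews ask arm II practices what became of their action plans. This limits the damage and is why the point is minor. A descriptive table would still show the rise without saying where it came from, and the interviews do not correct the tabulated item.

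**Conclusion.** The point holds for one secondary item. As described, the staff-education indicator cannot separate delivery of the workshop from a change in what the practice does, and this affects arm II only. The conclusion assumes that the workshop lies in the follow-up look-back year, that respondents count it, and that the form carries no exclusion.

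Under full delivery the built-in difference from control is 1 − *p*: 70 points at a control rate of 30%, but only 10 points at 90%. Since neither the baseline nor the control rate is given, no single size can be stated, and an inevitable improvement in arm II cannot be claimed. The team-meeting frequency is affected by about one occasion at most. The primary endpoint, its Poisson analysis and its power are unaffected. This is a cheap improvement of minor severity.

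**What to change.** Keep the existing education and meeting items at follow-up, so that the comparison with baseline stays like for like. Add two questions to the follow-up practice questionnaire, worded identically in all three arms:

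- apart from sessions organised by the study, was safety a subject of staff education in the past year;
- apart from such sessions, how many times was safety discussed in team meetings.

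Base any statement about an effect on the added answers.

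If the follow-up forms have already gone out, report the arm II education item as intervention delivery and do not interpret it as an effect.

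The cost is two short questions on a form that is already planned. There are two small downsides. The added questions have no exactly worded baseline counterpart. A practice that let the workshop take the place of its own safety education would answer no, which pulls the item the other way. Showing the existing and the added answers side by side lets the reader see both.
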